## Abstract

**Introduction::**

Uterine fibroids is a common benign tumor disease of the female reproductive system. The main methods of current clinical treatment of uterine fibroids are conservative treatment and surgical treatment. With the rise of the concept of minimally invasive surgery in gynecology, laparoscopic myomectomy, and vaginal myomectomy have been widely used.

**Methods/design::**

This study plans to retrospectively analyze 150 patients with uterine fibroids. They will be divided into laparoscopic myomectomy, vaginal myomectomy group, and open hysteromyoma resection group. This study will compare the intraoperative blood loss, operation time, postoperative exhaust time, postoperative hospital stay and postoperative complications of different surgical methods.

**Discussion::**

This study will compare the clinical efficacy of these 3 common surgical methods through retrospective medical record analysis, and provide more reliable evidence-based medical evidence for clinical treatment choices.

## Introduction

1

In recent years, the incidence of uterine fibroids has been on the rise. Myomectomy is an ideal surgical procedure to preserve female fertility.^[1]^ Uterine fibroids are common benign tumor diseases of the female reproductive system, which mostly occur in young and middle-aged women. The clinical incidence of this disease can reach 20%.^[2]^ Uterine fibroids can easily lead to uterine enlargement, menstrual disorders, vaginal bleeding, etc, and often cause infertility in women during reproductive periods. In addition, long-term vaginal bleeding easily induces secondary anemia, which affects the patient's quality of life and life safety. At present, the main methods of clinical treatment of uterine fibroids are conservative treatment and surgical treatment. With the rise of minimally invasive concepts in gynecological surgery, laparoscopic myomectomy and vaginal myomectomy have been widely used. Laparoscopic myomectomy has the advantages of low invasiveness, high curative effect, and high aesthetics,^[3]^ and is widely used in clinical practice. Nowadays, vaginal myomectomy is a newly emerged gynecological minimally invasive surgery method,^[4]^ due to its short operation time and intraoperative bleeding The advantage of small amount is a common minimally invasive procedure of myomectomy. Although the traditional open hysteromyoma resection has a large abdominal wall incision, slow recovery of the body, and a longer hospital stay, it still has an irreplaceable position in surgical procedures with larger tumors and longer gestational weeks. This study will compare and analyze the clinical effects of the above 3 surgical methods, and explore practical and effective clinical surgical programs.

## Methods/design

2

### Study design and settings

2.1

This study is a retrospective clinical trial. At present, we have completed the pre-registration (ChiCTR2100053314) at the China Clinical Trial Center. The time points for registration and evaluation are shown in the standard protocol project: Intervention Trial Recommendation chart (Fig. 1).

**Figure 1 F1:**
[figure not shown]
SPIRIT figure for the schedule of enrollment, interventions, and assessments. SPIRIT = Standard Protocol Items: Recommendations for Interventional Trials.

#### Diagnostic criteria

2.2.1

Common clinical symptoms of uterine fibroids include increased menstrual flow and prolonged menstrual periods, larger fibroids, palpable masses in the lower abdomen, increased leucorrhea, compression symptoms (including compression of the bladder, rectum, and ureters), and other symptoms (lower abdominal pain), Back pain), etc; Gynecological examination: the uterus is enlarged and the surface is uneven with single or multiple nodular protrusions; Auxiliary examination: vaginal ultrasound supports the diagnosis of uterine fibroids; Postoperative disease Physical examination is the gold standard for diagnosis: the pathological section after resection confirms the diagnosis of uterine fibroids. Diagnosed as uterine fibroids through the above symptoms, signs and auxiliary examinations.

#### Eligibility criteria

2.2.2

Female patients between 40 to 50 years old;The uterus enlarges to the size of 8 to 20 weeks of pregnancy;There is no contraindication to surgery, and the operation method is Laparoscopic myomectomy or Vaginal myomectomy or open hysteromyoma resection;All surgeons are doctors with rich clinical experience at the level of deputy chief physician or above;Complete clinical data;

The exclusion criteria are as follows:

Past pelvic and abdominal surgery history;Severe pelvic adhesions;Combined diseases that significantly affect surgery and prognosis, such as diabetes, hypertension, heart disease, liver, kidney, and other important organ complications;With a history of gynecological malignant tumors or other tumors;History of blood disease;History of taking anticoagulant drugs;Severe vaginal inflammation;Combined with other non-pelvic surgery cases, such as appendectomy, etc;Laparoscopy and vaginal hysterectomy were converted to open surgery.

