Laparoscopic myomectomy has the advantages of small incision, less postoperative pain, less interference to the abdominal cavity, faster postoperative recovery, and shorter hospital stay. At the same time, its pelvic vision is clear, which is conducive to comprehensive observation of abdominal organs and pelvic adhesions. However, the operation is complicated, and it is suitable for uterine fibroids patients with fibroids ≥4 cm in diameter but ≤10 cm in single or multiple (<4). Uterine fibroids with a diameter of more than 10 cm or more than 4 uterine fibroids are considered to be contraindications for laparoscopic surgery,^[7]^ which may increase the amount of intraoperative bleeding and increase the difficulty of suture. Since fibroids cannot be directly touched, the experience and skills of the surgeon have a great influence on the results of the operation, and fibroids with smaller diameters are likely to be missed, resulting in recurrence of the disease. In addition to the advantages of laparoscopic surgery, Vaginal myomectomy compresses the blood vessels of the uterus due to the extreme flexion or flexion of the uterus, which reduces the amount of bleeding and makes up for the shortcomings of laparoscopic surgery. At the same time, vaginal myomectomy takes advantage of the feature that the uterus and vagina are connected to the outside world, and there is no scar on the abdominal wall after the operation to relieve the pain of the patient.

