Vaginal myomectomy is easy to cause postoperative hematoma, the formation rate is 11%, and the open-abdominal type is only 8%.^[8,9]^ The 3 surgical methods analyzed in this project have their own points and shortcomings. Open hysteromyoma resection has the widest range of application, with fewer contraindications, and is irreplaceable clinically. However, the amount of bleeding during open hysteromyoma resection is higher than other surgical methods. Laparoscopic myomectomy has many advantages, but the operation is complicated and the operation time is longer. Vaginal myomectomy has the advantages of the laparoscopic group, its intraoperative blood loss was significantly lower than that of the laparoscopic group, and the operation time was also less than that of the laparoscopic group. Vaginal myomectomy is more advantageous than the open and laparoscopic groups in its indications. However, the number of fibroids is generally not more than 2. For larger fibroids, it needs to be minced and then removed, which also increases the risk of intraoperative bleeding. At the same time, with the improvement of technology and equipment, laparoscopic assisted vaginal myomectomy combines the advantages of both, and at the same time expands the indications of laparoscopic myomectomy, providing more options for replacing open abdominal. This study intends to compare the clinical efficacy of these 3 common surgical methods through retrospective medical record analysis, and to provide more reliable evidence-based medical evidence for clinical treatment choices.

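### Entry criteria set no limit on fibroid diameter or number, so the open group can include women with few or no counterparts in the laparoscopic and vaginal groups

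*Protocol article*

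**What the plan says.** Section 2.2.2 applies one size criterion to all three groups: "The uterus enlarges to the size of 8 to 20 weeks of pregnancy". It also requires that "There is no contraindication to surgery, and the operation method is Laparoscopic myomectomy or Vaginal myomectomy or open hysteromyoma resection". Neither criterion mentions the diameter, number or location of fibroids. The exclusion list does not either, although it removes laparoscopic and vaginal cases that were converted to open surgery.

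Section 3 (Discussion) describes the reach of each route:

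- Laparoscopic: suitable from 4 to 10 cm with fewer than 4 fibroids. Beyond that, "Uterine fibroids with a diameter of more than 10 cm or more than 4 uterine fibroids are considered to be contraindications for laparoscopic surgery".
- Vaginal: "the number of fibroids is generally not more than 2". Larger fibroids can be removed in pieces, as section 2.3 also provides.
- Open: "Open hysteromyoma resection has the widest range of application, with fewer contraindications, and is irreplaceable clinically". The Introduction adds that it cannot be replaced where tumors are larger or the uterus corresponds to a later gestational week.

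Section 2.2 forms the groups by the operation performed, with 50 cases in each. Section 2.5 compares them with t, rank-sum, chi-square and analysis-of-variance tests at P ≤ .05. It names no matching and no covariate for fibroid burden.

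**The concern.** The study is meant to inform the choice among three operations. That calls for women for whom at least two of the operations were realistic options. By the protocol's own account, large or numerous fibroids tend to go to open surgery, and nothing in section 2.2.2 keeps such women out of the open group or requires comparable women in the other two.

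The Discussion itself links large or numerous fibroids to more bleeding and harder suturing at laparoscopy, so fibroid burden plausibly affects blood loss and operation time, two of the outcomes in section 2.4. The Discussion already states that open surgery bleeds more. An unadjusted comparison could reproduce that result from case mix alone. Excluding conversions pushes the same way, because it removes difficult cases from the laparoscopic and vaginal groups only.

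**Working it through.** **Step 1: entry criteria against the stated range of each route.** All the profiles below can enter under section 2.2.2 if the uterus is within 8 to 20 weeks' size.

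| Fibroid profile | Laparoscopic (Discussion) | Vaginal (2.3, Discussion) | Open |
|---|---|---|---|
| 1–2 fibroids, 4–10 cm | within range | within usual number | yes |
| 3 fibroids, 4–10 cm | within range | above usual number | yes |
| exactly 4 fibroids | not defined (suitable below 4, contraindicated above 4) | above usual number | yes |
| more than 4 fibroids | contraindicated | above usual number | yes |
| 1–2 fibroids, over 10 cm | contraindicated | possible after fragmentation | yes |

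The clearest stratum short of counterparts in both other groups is more than 4 fibroids. Fibroids over 10 cm lack laparoscopic counterparts but can have vaginal ones. The first two rows are regions of real overlap.

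**Step 2: does the contraindication criterion close the gap?** It has three possible readings:

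- General fitness for surgery: this sets no fibroid limit.
- No contraindication to the operation received: this limits the laparoscopic group and leaves the open group unrestricted.
- No contraindication to any of the three routes: this would largely close the gap, but the text does not say it.

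**Step 3: illustration of size.** The protocol states no effect size, SD or power, so there is no figure of its own to reproduce. The only check is 3 × 50 = 150, which agrees with the Abstract.

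Inputs from the protocol: n = 50 per group and a significance level of 0.05 (two-sided assumed, since sidedness is not stated). Assumed inputs, not in the documents: a share q of the open group has no counterpart and has an outcome worse by D SD, and the true effect of route is zero.

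- Shift in the open mean = q × D
- Open-group variance = 1 + q(1 − q)D²; the other group's variance = 1
- SE = √[(average of the two variances) × 2/50]
- Chance of P ≤ .05 = Φ(shift/SE − 1.96) + Φ(−shift/SE − 1.96)

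Low case, q = 0.2, D = 0.5: shift 0.10; open variance 1 + 0.16 × 0.25 = 1.04; SE = √(1.02 × 0.04) = 0.202; ratio 0.495; chance about 8%.

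Middle case, q = 0.3, D = 1: shift 0.30; open variance 1.21; SE = √(1.105 × 0.04) = 0.210; ratio 1.43; chance about 30%.

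High case, q = 0.5, D = 1: shift 0.50; open variance 1.25; SE = √(1.125 × 0.04) = 0.212; ratio 2.36; chance about 65%. Ignoring the extra variance of a mixed open group would give about 70%, which is too high.

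The nominal rate is 5%.

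**The case against.** Five objections deserve weight.

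- **No case mix is given.** A reader might infer that the open group does contain women with no comparable case. The Introduction and Discussion make this likely but do not show it. The supported statement is that it can.
- **Large fibroids are not barred from the vaginal route.** Sections 2.3 and 3 provide for fragmentation, and the limit on number is a tendency rather than a contraindication. Reading the protocol as ruling out vaginal removal of large fibroids would be wrong.
- **The laparoscopic limits are background.** They stand in the Discussion and rest on a cited source. Nothing says the hospital's surgeons followed them over the 5 years, and laparoscopic charts beyond those limits may exist.
- **The groups share real restrictions.** These include age 40 to 50, uterine size of 8 to 20 weeks, and exclusions for earlier pelvic or abdominal surgery, severe adhesions and major comorbidity. A reader might conclude that the groups are three separate populations by construction and that adjustment is useless. The documents do not support that. Women with 1 to 3 fibroids of 4 to 10 cm lie within both the open and the laparoscopic range, and matching or adjustment works there. Only the part without overlap would need extrapolation, and its extent is unknown.
- **Adjustment may be set out in an analysis plan not shown.** That is possible. But eligibility is fixed in the protocol, and the stated criteria do not fit the protocol's own account of who receives which operation.

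These points narrow the concern. None supplies the missing limit on fibroid diameter or number, or a rule that makes the groups comparable on them.

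**Conclusion.** The concern holds in limited form. Section 2.2.2 admits women whom the Discussion places outside the laparoscopic range and the usual vaginal range. Allocation by operation received, followed by unadjusted tests, can then turn a difference in fibroid burden into an apparent effect of route. More than 4 fibroids is the clearest such stratum.

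Under the assumed shares (20% to 50%) and shifts (0.5 to 1 SD), the chance of a nominally significant open-versus-other difference with no true effect is about 8% to 65%. The width of that range reflects how little the documents say about case mix. It is an illustration and not an estimate of the bias in this study. The point should be settled before charts are selected, and section 2.7 indicates that recruitment has not started and that ethics review is still to come.

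**What to change.** 1. Extract preoperative fibroid diameter, number and location for every screened chart.
2. For each pairwise comparison, restrict both groups by the same rule to women who were candidates for both operations, and match or adjust on these three variables within that overlap. Pairwise restriction keeps, for example, open-versus-laparoscopic comparisons in women with 3 fibroids, which requiring candidacy for all three routes would discard.
3. Describe the remaining open cases separately, without comparative tests.
4. The investigators need to reconcile section 2.2.2 with the limits in the Discussion. This includes the undefined case of exactly 4 fibroids, and whether the contraindication criterion refers to general fitness, the operation received or all routes. Which limits apply is a clinical decision for them.

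The cost is a change to the eligibility and analysis wording, three more variables to extract, and more charts to screen in the 5-year window to fill the groups. Conclusions would apply only to women eligible for the operations being compared.

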### Interventions

2.3

Use iodophor cotton ball to sterilize the vagina for 3 days, 2 times a day before surgery; clean the enema the night before surgery and fast water for at least 8 hours; general anesthesia for laparoscopic myomectomy, combined spinal-epidural anesthesia or general anesthesia for vaginal myomectomy and open hysteromyoma resection.

Laparoscopic myomectomy group: take the bladder lithotomy position, insert a pneumoperitoneum needle just above the umbilical edge, insert a 10 mm umbilical puncture cannula, insert a laparoscope, CO_2_ pneumoperitoneum, pneumoperitoneum pressure 12 to 13 mm Hg, after the pneumoperitoneum is completed, Routine 3-point puncture in the abdomen, puncture cannula diameter 5 mm, uterine body injection of oxytocin, according to the size, location, direction of the uterine fibroids, cut the surface membrane of the fibroids, separate the tumor body, while using electrocoagulation to stop bleeding. The muscular layer of the tumor cavity was sutured first, and then the seromuscular layer was sutured, and the drainage tube was indwelled for 24 hours after the operation.Vaginal myomectomy group: take the bladder lithotomy position, choose the vaginal vault incision according to the tumor position, cut the vaginal mucosa, advance to the front and back of the uterus, incise the peritoneum, and expose the uterus, cut the surface membrane of the fibroids, and separate the tumor body, if the fibroids are too large, the tumors will be removed after fragmentation. Routine stitching after removal.Open hysteromyoma resection group: According to the routine open myomectomy operation.

### Outcomes

2.4

The choice of outcome indicators will be evaluated according to the amount of blood loss, operation time, postoperative exhaust time, postoperative hospital stay and postoperative complications. In addition, we will calculate the recurrence rate of uterine fibroids through follow-up.

### Statistical analysis

2.5

Data management uses EXCEL software to build a database, double entry, check for outstanding values, and lock. Statistical analysis will be performed using SPSS 25.0 software for statistical analysis. The normality of the measurement data is tested. The data obeying the normal distribution is Student *t* test, which is expressed by mean ± standard deviation. The data not obeying the normal distribution is rank sum test. And marginal homogeneity test; count data are expressed by rate and composition ratio, and comparison is performed by chi-square test; repeated measurement data are expressed by mean ± standard deviation, intra-group comparison is performed by analysis of variance of repeated measurement data, and inter-group comparison is by multivariate analysis of variance. *P* ≤ .05 indicates that the difference is statistically significant.

### Data management

2.6

Information obtained from the evaluation of each participant will be recorded on a paper print-out. The information will then be handwritten on a paper document case report form and entered into an Excel file for future statistical analyses. In accordance with the Personal Information Protection Act, the names of all participants will not be disclosed, and a unique identifier number given during the trial will be used to identify participants. All of the participants will be informed that the clinical data obtained in the trial will be stored in a computer and will be handled with confidentiality. The participants’ written consent will be stored by the principal investigator.

### Ethics

2.7

The study will be conducted under the Declaration of Helsinki principles, as well as following the norms of good clinical practice. Recruitment of patients has not started in this study. The study plan will be submitted to the ethics committee of the Second Affiliated Hospital of Shaanxi University of Traditional Chinese Medicine for review. The final study version will be approved by the Ethics Committee of the Second Affiliated Hospital of Shaanxi University of Chinese Medicine. We will not include subjects without the approval of the ethics committee.

## Discussion

3

Uterine fibroids is one of the common benign tumors in female gynecology, with a higher incidence in women aged 30 to 50. The cause of uterine fibroids is currently unclear, and may be affected by estrogen and progesterone in the receptor.^[5]^ Common symptoms include uterine bleeding, mass and compression symptoms in the abdomen, and a few painful phenomena. Some uterine fibroids may have no symptoms. Common treatments include medications such as mifepristone, uterine artery embolization and surgical treatment, of which surgical treatment is the main one. However, myomectomy is widely used as an ideal surgical method for preserving female fertility. At the same time, this surgical method has little effect on the patient's hypothalamic-pituitary-uterine axis, which is beneficial to the patient's postoperative recovery. Since 1844, the first successful implementation of Open hysteromyoma resection, due to the corresponding complications, this surgical method was not widely used until the middle of the 20th century.^[6]^ Open hysteromyoma resection is now relatively mature. With the development of the concept of minimally invasive, laparoscopic myomectomy and vaginal myomectomy are now widely accepted, and gradually replace open hysteromyoma resection.

Laparoscopic myomectomy has the advantages of small incision, less postoperative pain, less interference to the abdominal cavity, faster postoperative recovery, and shorter hospital stay. At the same time, its pelvic vision is clear, which is conducive to comprehensive observation of abdominal organs and pelvic adhesions. However, the operation is complicated, and it is suitable for uterine fibroids patients with fibroids ≥4 cm in diameter but ≤10 cm in single or multiple (<4). Uterine fibroids with a diameter of more than 10 cm or more than 4 uterine fibroids are considered to be contraindications for laparoscopic surgery,^[7]^ which may increase the amount of intraoperative bleeding and increase the difficulty of suture. Since fibroids cannot be directly touched, the experience and skills of the surgeon have a great influence on the results of the operation, and fibroids with smaller diameters are likely to be missed, resulting in recurrence of the disease. In addition to the advantages of laparoscopic surgery, Vaginal myomectomy compresses the blood vessels of the uterus due to the extreme flexion or flexion of the uterus, which reduces the amount of bleeding and makes up for the shortcomings of laparoscopic surgery. At the same time, vaginal myomectomy takes advantage of the feature that the uterus and vagina are connected to the outside world, and there is no scar on the abdominal wall after the operation to relieve the pain of the patient.

Vaginal myomectomy is easy to cause postoperative hematoma, the formation rate is 11%, and the open-abdominal type is only 8%.^[8,9]^ The 3 surgical methods analyzed in this project have their own points and shortcomings. Open hysteromyoma resection has the widest range of application, with fewer contraindications, and is irreplaceable clinically. However, the amount of bleeding during open hysteromyoma resection is higher than other surgical methods. Laparoscopic myomectomy has many advantages, but the operation is complicated and the operation time is longer. Vaginal myomectomy has the advantages of the laparoscopic group, its intraoperative blood loss was significantly lower than that of the laparoscopic group, and the operation time was also less than that of the laparoscopic group. Vaginal myomectomy is more advantageous than the open and laparoscopic groups in its indications. However, the number of fibroids is generally not more than 2. For larger fibroids, it needs to be minced and then removed, which also increases the risk of intraoperative bleeding. At the same time, with the improvement of technology and equipment, laparoscopic assisted vaginal myomectomy combines the advantages of both, and at the same time expands the indications of laparoscopic myomectomy, providing more options for replacing open abdominal. This study intends to compare the clinical efficacy of these 3 common surgical methods through retrospective medical record analysis, and to provide more reliable evidence-based medical evidence for clinical treatment choices.
